### 6.2.2 Research Question 1b: Average Pain Intensity at the End of Treatment

If the result of the analysis of research question 1a indicates a significant effect of briefing on the expectations of acupuncture treatment, research question 1b will be analysed. The pain intensity will be analyzed using ANCOVA. Outcome variable is the pain intensity (`nrs_8_1`) measured at the end of the acupuncture treatment. Covariate of interest is the effectiveness briefing group (`EXPBRIEF`). As adjustment variables, pain intensity at first visit (`screening_1a_4a`), gender (`pers_1_2`), acupuncture therapist (`acupuncturist`), and baseline optimism (`LOT_BL_optim`) and pessimism (`LOT_BL_pessim`) will be used.

Missing values will be imputed (see Section 6.5). As a sensitivity analysis, the same model will be fitted again, using only complete cases (see Section 6.4). The estimated mean difference of the two briefing groups with 95% confidence interval and  $p$ -value will be reported. The estimated effects of the adjusting variables will not be shown. In addition, adjusted means with 95% confidence intervals will be reported for each treatment group, where all continuous adjustment variables will be fixed at their mean, and the effects of acupuncture therapist and gender will be given equal weights over the factor levels (thus 0.5 for gender and 0.33 for acupuncturist).

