### 3.2 Randomization

Block-randomization with randomly varying block sizes (either 4 or 8) in a 1:1:1:1 ratio was used. An additional block will be used at the beginning that is not balanced, this means that the final totals in each group may not be exactly equal (but still similar). This made it more difficult to anticipate future assignments as the numbers will not return to equality at the end of each block (Schulz and Grimes, 2002). The randomization sequence was stratified by gender using R (version 3.1.0). For allocation of patients via the internet, the software secuTrial® (Clinical Trial Center, University Hospital Zurich) was used.

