#### 3.3.1 Research Question 1a

No previous data on expectancy change were available for trial planning purposes. For this study, the assumption was that the high expectation briefing is clinically meaningful better than a regular expectancy briefing in changing expectation, with a standardized mean difference (SMD) of 0.5. Assuming a power of 80% and a two-sided alpha level of 5%, a sample size of 128 patients (64 high expectation briefing and 64 regular expectation briefing) would enable the detection of a difference of SMD 0.5 for the expectancy briefing intervention. Assuming a dropout rate of approximately 15%, 150 patients were sought to be enrolled.

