#### 3.3.2 Research Question 1b

With the above mentioned sample size the power is 56–65% ( $n = 128$ –150) to detect a significant difference between high and regular expectation briefing on pain intensity after the acupuncture treatment. This assumption is based on a previous study (Linde et al., 2007) with response rates of 54% in the high expectation group and 39% in the low expectation group that resulted in a SMD of 0.38.

### 3.3.3 Research Question 2

Variation of the outcomes was not known prior to the study. Thus, the sample size was determined using two-group Fisher's exact tests of equal proportions (for binary outcomes). 50% of the patients in the intense safety briefing group and 10% in the regular group were expected to have side effects such that a side effects score can be calculated (Witt et al., 2009). It showed that with 64 patients in each study group such differences in outcome scores could be detected with at least 99% power at a 0.05 two-sided significance level. This power analysis was conservative and the actual power of the study will be higher since a count score and not a binary variable is used.

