## 4 Statistical Principles

### 4.1 Confidence Intervals and $p$ -Values

All confidence intervals are 95% and two-sided. All tests are two-sided and performed at a significance level of 0.05.

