### **3.3 Clinical Evidence to Date**

#### **Expectation:**

Research shows that expectations of clinical improvements in pain play the most important role for the placebo response (Enck, Benedetti, & Schedlowski, 2008). Larger expected benefits of a treatment go along with larger effects of treatments across different medical conditions (Mondloch, Cole, & Frank, 2001).

In cohort studies, patients' positive expectations have been shown to decrease pain after medical treatment (Bialosky et al., 2010; Bishop et al., 2014; Iles et al., 2009). Patient expectations also affect the acupuncture treatment effect. A pooled analysis of our previous acupuncture trials including more than 800 patients with chronic pain showed that patients' expectations predicted acupuncture treatment response (Linde et al., 2007). Patients had higher odds (odds ratio 2.11 [CI 1.32 – 3.34]) of benefitting from acupuncture if they expected a better treatment response before the intervention. This finding holds for regular acupuncture as well as for sham acupuncture.

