### **11.3.2 Primary Analysis**

The significance level will be set to  $\alpha = .05$ . It will be tested two-sided.

For the first hypotheses (1a) we will use an analysis of covariance (ANCOVA) with the fixed effects briefing group and sex and the covariate baseline expectation to determine the difference on expectation (EAT score) before the first acupuncture treatment between both briefing interventions.

For the second hypotheses (1b) to determine the difference in pain (numeric rating scale) after 4 weeks of acupuncture treatment we will use ANCOVA with the fixed effects briefing group, sex, therapist and the covariates baseline pain and optimism.

We use this hierarchical test procedure to control for multiple testing. In a first step, we will test if the briefing changes the expectation. Only if the null hypothesis 1a was rejected (high expectation briefing  $\neq$  regular expectation briefing) we will test in a second step whether the briefing changes pain after treatment (hypotheses 1b), using the same alpha level.

Sensitivity analyses for both analyses will include a.) adding various covariates to the model (e.g. age, duration of disease, depression, empathy), b.) changing the study populations (per-protocol), and c.) using different multiple imputation methods for missing data (hot deck and regression methods). Confidence intervals and p-values from sensitivity analyses are

considered explorative. The research question if briefing effects on pain are mediated by initial treatment expectations will be tested according to the framework suggested by Baron and Kenny (Baron & Kenny, 1986; Hayes, 2009) in a hierarchical regression analysis.

Research question 2: As primary analysis, the total side effect score after 8 sessions will be compared between safety briefing groups using zero-inflated and hurdle models for count data. This analysis will require to appropriately imputing intermittent missing side effect scores and dropouts. Alternatively, a longitudinal analysis of the side effect scores, available from up to 8 sessions, will be achieved through an appropriate model extension using patient-specific random effects. As no standard software is available for this, problem-specific implementation using Markov Chain Monte Carlo (MCMC) or INLA ([www.r-inla.org](http://www.r-inla.org)) will be used. Analyses will be conducted after LPLV by the statistician, presumably in the third year of the project.

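### The research question 1b pain model omits baseline treatment expectation (EAT_BL), a pre-briefing covariate the trial already collects: a small loss of precision, with no effect on validity

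*Combined protocol and SAP*

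**What the plan says.** **Primary 1b model.** SAP 6.2.2 specifies an ANCOVA of pain after session 8 (nrs_8_1) on effectiveness briefing. It adjusts for pain at first visit, gender, acupuncturist, "and baseline optimism" and pessimism. Protocol 11.3.2 gives nearly the same set: "fixed effects briefing group, sex, therapist and the covariates baseline pain and optimism". Neither includes baseline expectation.

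**Related models and lists.**
- The extended model (SAP 6.4.3) adds age, pain duration, depression and CARE, but not EAT_BL.
- The imputation predictors for 1b (SAP 6.5) and for follow-up pain (SAP 6.6.5) also leave it out.
- The week-2 and follow-up pain models (SAP 6.6.2, 6.6.5) take their covariates from 6.2.2, so they inherit the omission.

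**Availability.** SAP 6.1 has the expectation questionnaire completed at baseline, before the briefing. Appendix B lists EAT_BL with range 5–20. It is a covariate and an imputation variable for 1a (SAP 6.2.1, 6.5).

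**Premise.** Protocol 3.3 reports from a pooled analysis that patients' "expectations predicted acupuncture treatment response", with an odds ratio of 2.11 (CI 1.32–3.34). SAP 3.3.2 takes the 1b effect size from response rates of 54% and 39% in high- and low-expectation patients "that resulted in a SMD of 0.38", and states power of 56–65% for n = 128–150.

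**The concern.** A covariate measured before the intervention that predicts the outcome reduces residual variance and narrows the confidence interval for the treatment effect. The trial's rationale is that expectation of this treatment predicts response to it. The 1b model adjusts for general optimism and pessimism, for which the documents quote no comparable figure, and leaves out the more specific measure. Randomization is stratified by gender only, so nothing in the design balances baseline expectation.

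At stake is some precision on the primary outcome with the lowest planned power. EAT_BL could also help impute missing 1b pain scores, since about 15% dropout was expected.

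**Working it through.** **Inputs from the documents**
- Level (SAP 4.1): "All tests are two-sided and performed at a significance level of 0.05".
- Patients needed (SAP 3.3.1): "a sample size of 128 patients (64 high expectation briefing and 64 regular expectation briefing"), so 64 per briefing level.
- Enrolment (SAP 3.3.1): "Assuming a dropout rate of approximately 15%, 150 patients were sought to be enrolled", so up to 75 per level.
- Allocation (SAP 3.2): "randomly varying block sizes (either 4 or 8) in a 1:1:1:1 ratio", so 1:1 on the effectiveness factor.
- Effect (SAP 3.3.2): SMD 0.38. This is the probit difference of the two response rates: 0.100 − (−0.279) = 0.38.

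**Input not in the documents**
- The partial correlation r of EAT_BL with nrs_8_1, given the covariates already in the model. I assume 0.1 to 0.3.

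**Step 1: reproduce the stated power.** Two-sided two-sample t test, no covariates, noncentrality δ = 0.38 × √(n/2) with n per arm:
- n = 64: δ = 0.38 × √32 = 2.150, power 56.9% (stated 56%).
- n = 75: δ = 0.38 × √37.5 = 2.327, power 63.8% (stated 65%).

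Both agree within 2 points. The stated figure is therefore the power of an unadjusted comparison, taken for 1b alone.

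**Step 2: what r might be.** If the SMD of 0.38 came from equal-sized high and low groups and carries over to this trial:
- Expectation as a two-group variable: r = d/√(d² + 4) = 0.38/√4.1444 = 0.187, r² = 0.035.
- Expectation as a continuous normal score cut at its median, where the two halves lie 1.596 SD apart: r = 0.38/1.596 = 0.238, r² = 0.057.

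That is 3.5–5.7% of outcome variance, or about 150 × 0.035 = 5 to 150 × 0.057 = 9 patients' worth of information.

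**Step 3: power after adding EAT_BL.** The residual SD is multiplied by √(1 − r²), so the effect becomes 0.38/√(1 − r²), with one degree of freedom fewer.

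| Assumed r | √(1 − r²) | Power, n = 128 | Power, n = 150 |
|---|---|---|---|
| none (unadjusted) | 1.000 | 56.9% | 63.8% |
| 0.10 | 0.995 | 57.3% | 64.2% |
| 0.19 | 0.982 | 58.4% | 65.3% |
| 0.24 | 0.971 | 59.4% | 66.3% |
| 0.30 | 0.954 | 60.9% | 67.8% |

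The standard error falls by 0.5% to 4.6%, and by about 2–3% at r = 0.19–0.24. Power rises by 0.4 to 4.0 points.

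**Step 4: starting from the planned ANCOVA.** If the existing covariates explain 20% of outcome variance (an assumption), power before adding EAT_BL is already about 66% (n = 128) and 73% (n = 150). Adding it at r = 0.19 gives about 68% and 75%. The increment is similar; the starting point is higher.

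**The case against.** The strongest reply is that nothing here is wrong. The 1b covariates follow the protocol's prespecified model, and each primary ANCOVA adjusts for the stratification factor and the outcome's own baseline. Further covariates are a matter of judgement. That stands: this is a missed efficiency, not an error.

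A reader might infer three stronger things that the documents do not support.
- *Chance imbalance in baseline expectation biases the 1b result.* Under randomization the standard error and confidence interval already allow for such imbalance. Adjustment narrows them; it removes no bias.
- *The SMD of 0.38 is the correlation needed.* It comes from responder rates by expectation group in an earlier pooled analysis. Nothing shows that the analysis used EAT, split patients equally, or adjusted for baseline pain and optimism. The two figures quoted from it are not the same measure of the link either: the rates give a crude odds ratio of (0.54/0.46)/(0.39/0.61) = 1.84, against the reported 2.11. Here, moreover, the briefing follows EAT_BL and is meant to change expectation, with boosters later, so the link with final pain may be weaker.
- *The criticised model has only 56–65% power.* That figure is unadjusted (Step 1).

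On imputation, the 1b list already holds every 1b analysis variable plus auxiliaries, and no bias from leaving out EAT_BL is shown. Protocol 11.3.2 also studies expectation and pain through a mediation analysis and an exploratory regression. Neither makes EAT_BL a covariate in the 1b test.

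What survives is that a collected pre-briefing variable, expected on the trial's own premise to be prognostic, is unused at almost no saving.

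**Conclusion.** The point holds as a minor efficiency gain. At SMD 0.38, EAT_BL would add about 0.4 to 4.0 points of power for r = 0.1–0.3, and about 1.5–2.5 points for r = 0.19–0.24. The wider range is an assumption. The narrower one also needs an equal high/low split and transfer from a study without the briefing. Overlap with baseline pain and optimism, or a briefing that overrides prior expectation, could make the gain smaller still. The planned 1b analysis remains valid without the change, and the change does not turn an underpowered comparison into an adequately powered one.

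**What to change.** Issue a dated SAP amendment before the statisticians see allocation. (The unblinding on 23 January 2018 in SAP 3.6 is disclosure to patients; SAP 3.1 keeps the statistical analysis blind.) In it:
- add EAT_BL as a covariate to the 1b ANCOVA (6.2.2) and the follow-up pain ANCOVA (6.6.5);
- add EAT_BL to the imputation predictors for both (6.5, 6.6.5);
- do not add EAT_1b, which is measured after the briefing and is the proposed mediator; adjusting for it would remove part of the effect under test.

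If the sponsor prefers to leave the primary model as it stands, EAT_BL can go into the extended model (6.4.3) and the imputation lists. If allocation has already been seen, report the added model only as a post hoc sensitivity analysis.

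The cost is one degree of freedom and no new data. SAP 4.2 reports that a few patients did not fill in the baseline questionnaire. In the study schedule, baseline expectation and optimism share form P1, so EAT_BL should add almost no missingness beyond that of the optimism scores. The missing values can be imputed as already planned for 1a.

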### 6.2.3 Research Question 2: Side Effects Score at the End of Treatment

As a primary analysis, the side effect scores that are available from up to 7 measurements (before each session, except session 1) will be compared between side effects briefing groups. Covariate of interest thus is the side effects briefing group (`SIDEBRIEF`). The side effect scores will be treated as counts, because they are expected to show a skewed distribution. Because each patient has up to 7 outcome values, a longitudinal zero-inflated negative binomial model will be used. This model will provide increased statistical power with respect to a model with total score as outcome, because it utilizes all outcomes of all patients.

In addition to the briefing group, the linear predictor of the model includes gender (`pers_1_2`) and the time of the measurement since the first session (in days, derived from session dates `verlaufdokua_1b`, `verlaufdokua_2`, ..., `verlaufdokua_8`) as additional fixed effects, and patient-specific random effects for the intercept and time, where the latter accounts for patient-specific dependencies (*i.e.* slopes) on time. The zero-inflation probability will modelled as dependent on `SIDEBRIEF`. The model will be fitted with the `glmmTMB()` function from the R package `glmmTMB` (Brooks et al., 2017). If this longitudinal mixed model fails to converge with the specification given here, the random effect for time will be removed, that is, the dependency on time is then assumed to be the same for all patients.

It will be assumed that missing side effect scores are missing at random (MAR), that is, missingness depends only on observed variables. Importantly, the longitudinal analysis allows for unbalanced data, thus MAR in the outcome is automatically properly accounted for and does thus not require any imputation (Ibrahim and Molenberghs, 2009).

The result from the zero-inflated negative binomial regression will be reported as the ratio of side effect scores (*i.e.*, as the *factor* by which the side effect score changes from regular to intense

side effects briefing) with 95% confidence interval and  $p$ -value. Note that, in this case, a ratio of 1 corresponds to the null hypothesis that there is no effect of `SIDEBRIEF` on the side effect scores. The estimated effects of the adjusting variables will not be shown.

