#### 6.4.2 Protocol-Deviations: Research Question 1b

Research question 1b will be repeated excluding the patients who used opioids. The analysis of research question 1b will also be repeated including only patients that had at least 6 of the 8 acupuncture treatment sessions.

#### 6.4.3 Extended Models: Research Questions 1a, 1b, and 2

All research questions (1a, 1b, and 2) will also be analyzed using an extended model including age (`age`), duration of pain (`painduration`), depression (`PROMIS_BL_depression.theta`), and CARE score (`CARE_1a_red1`) as additional covariates. Missing values will be imputed.

The follow-up pain intensity (see Section 6.6.5) will be re-analyzed with an extended model as well, including age (`age`), duration of pain (`painduration`), depression (`PROMIS_BL_depression.theta`), and CARE score (`CARE_1a_red1`) as additional covariates. Missing values will be imputed.

Confidence intervals and  $p$ -values from sensitivity analyses are considered explorative.

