### 6.6.2 Research question 1b

A second ANCOVA using the pain intensity obtained after the 4th acupuncture session (in week 2) as outcome will be performed. The covariates and adjusting variables will be as described in Section 6.2.2.

### 6.6.3 Research question 2

A secondary outcome for research question 2 is the total side effect score for each patient, which will be adjusted for the number of acupuncture sessions that the patient actually received minus 1. For a patient with the number of sessions given by  $N_s$ , the outcome is thus

$$\text{Total score} = \frac{(\text{Score}_1 + \text{Score}_2 \dots + \text{Score}_{N_s-1})}{N_s - 1} \cdot 7.$$

As this may lead to total score values that are non-integers, the total score will be rounded to the next integer. A zero-inflated negative binomial model with SIDEBRIEF and gender (`pers_1_2`) will be

used. As for the primary analysis (Section 6.2.3), the result from the zero-inflated negative binomial regression will be reported as the ratio of side effect scores with 95% confidence interval and  $p$ -value. In addition, adjusted means of the total side-effects scores with 95% confidence intervals will be reported for each treatment group, where the gender effect will be weighted with 0.5.

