### 6.6.6 Perceived Sensitivity to Medicines Score, PSM

The PSM score will be analyzed using three ANCOVA models (no imputation):

```
PSM_8 ~ SIDEBRIEF + pers_1_2 + PSM_BL
```

```
PSM_8 ~ SIDEBRIEF + pers_1_2 + LOT_BL_optim + LOT_BL_pessim +  
acupuncturist + PSM_BL
```

```
PSM_8 ~ SIDEBRIEF + pers_1_2 + LOT_BL_optim + LOT_BL_pessim +  
acupuncturist + age + painduration + CARE_1a_red1 + PSM_BL
```

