#### 9.2.2 Assessment of Secondary Outcomes

Back pain severity: assessed as a secondary outcome by a numeric rating scale NRS (0-10) at 2 weeks (short term impact).

The back pain bothersomeness will be assessed by a numeric rating scale NRS asking for the average back pain bothersomeness in the last 7 days (0-10).

Self-reported health: PROMIS 29 (Patient-Reported Outcomes Measurement Information System) (Cella et al., 2010; Fries et al., 2011; Liu et al., 2010; Rothrock et al., 2010) is a well validated measure that was developed from the National Institutes of Health (NIH) in the USA

and is also available also in German. The PROMIS 29 is suggested as standard measure for CLBP studies by NIH (Deyo et al., 2014). Its profile covers the dimensions of anxiety, depression, fatigue, pain interference, physical function, sleep disturbance, and ability to participate in social roles and activities. All domains encompass four items with the exception of pain, which is measured by a single item. It will be measured at baseline, after 2 and 4 weeks of acupuncture and at the 6 months follow-up.

Working alliance with the acupuncturist: We will use 4 items of the Working Alliance Inventory (WAI-SR), (Wilmers et al., 2008) which measure the outcome on a 5 point scale. It will be measured after the first and the last acupuncture session.

We use the Perceived Sensitivity to Medicines Questionnaire (PSM), (Horne et al., 2013) to assess the belief to be influenced by medicines and experience side effects. It will be measured with 5 items on a 5 point Likert scale at baseline and at the end of the study.

Pain rescue medication (Brinkhaus et al., 2006): We will use a weekly diary to document the use of pain continuously. Patients will receive each week a new week-diary.

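### Cheap improvement, not an error: no question 2 model adjusts for baseline Perceived Sensitivity to Medicines (PSM_BL), although the trial already collects it before randomisation

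*Combined protocol and SAP*

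**What the plan says.** Three models address the side effects score, and none contains PSM_BL.

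- **Primary longitudinal model (SAP 6.2.3).** Beyond briefing group, "the linear predictor of the model includes gender (`pers_1_2`) and the time of the measurement since the first session", with patient-specific random intercepts and slopes. The zero-inflation part depends on briefing group alone.
- **Total-score model (SAP 6.6.3).** "A zero-inflated negative binomial model with SIDEBRIEF and gender", and no other covariate.
- **Extended model (SAP 6.4.3).** The list is "including age (`age`), duration of pain (`painduration`), depression (`PROMIS_BL_depression.theta`), and CARE score". It is applied to questions 1a, 1b and 2 alike, and missing values are to be imputed.

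Protocol 9.2.2 says that the PSM questionnaire is used "to assess the belief to be influenced by medicines and experience side effects", at baseline and at the end of the study. Its only modelled use in the SAP is for its own follow-up value in 6.6.6, for example "PSM_8 ~ SIDEBRIEF + pers_1_2 + PSM_BL".

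By contrast, question 1a adjusts for baseline expectation (SAP 6.2.1). Question 1b adjusts for pain at first visit, therapist, optimism and pessimism (SAP 6.2.2). The protocol's own paragraph on question 2 (11.3.2) names no covariates, and the SAP gives no reason for leaving PSM_BL out.

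**The concern.** Each patient gives up to 7 side effect scores. Averaging over sessions reduces the noise within a patient but not the differences between patients in how many side effects they report. Those differences may therefore dominate the uncertainty of the briefing ratio. A baseline variable that predicts them would narrow the confidence interval and correct for chance imbalance on that variable.

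Gender, the stratification factor, is the only baseline covariate in the primary question 2 model. PSM_BL is an obvious candidate to join it, since by the protocol's description it concerns beliefs about experiencing side effects and it is measured before the briefing. The extended model, by comparison, takes in CARE, which patients complete after the briefing (protocol 9.2.3 and 9.3.2), but not PSM_BL.

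At stake is the width of the reported 95% interval, and power if the true effect is much smaller than planned.

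**Working it through.** **1. The plan's own power figure.** Inputs from SAP 3.3.3: 64 patients per group, two-group Fisher's exact test, and "50% of the patients in the intense safety briefing group and 10% in the regular group were expected to have side effects". From SAP 4.1: "All tests are two-sided and performed at a significance level of 0.05".

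Exact power = sum over all i, j of Bin(i; 64, 0.50) × Bin(j; 64, 0.10), counting only the tables with Fisher p ≤ 0.05. Result: 0.9991. The plan says at least 99%, so the figure is reproduced. By the normal approximation, 44 per group would already give 99% power (48 with continuity correction).

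**2. Is PSM_BL measured before randomisation?** The protocol's study schedule places baseline PSM on form P1. P1 is mailed after the telephone screening (9.3.1) and handed in at visit 1a, before allocation and briefing (9.3.2). It is therefore a proper baseline covariate. SAP 4.2 notes that a few patients did not complete the baseline questionnaire.

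**3. Size of the gain.** Two quantities are needed and the documents give neither; SAP 3.3.3 says that the variation of the outcome was unknown. Both are assumptions here:

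- r, the correlation of PSM_BL with a patient's log side-effect level: 0 to 0.4;
- s, the share of the variance of a patient's mean that lies between patients: 0.8, with 1 as the ceiling.

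SE factor = sqrt(1 − s·r²). Equivalent extra patients on 150 = 150 × [1/(1 − 0.8·r²) − 1].

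For r = 0.3: sqrt(1 − 0.8 × 0.09) = sqrt(0.928) = 0.963, and 150 × (1/0.928 − 1) ≈ 12.

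| r | SE factor, s = 0.8 | Fall in SE | Fall at ceiling s = 1 | Extra patients on 150 | Model-SE ratio, simulation A | Model-SE ratio, simulation B |
|---|---|---|---|---|---|---|
| 0 | 1.000 | 0% | 0% | 0 | not run | 1.002 |
| 0.2 | 0.984 | 1.6% | 2.0% | 5 | 0.989 | 0.990 |
| 0.3 | 0.963 | 3.7% | 4.6% | 12 | 0.973 | 0.974 |
| 0.4 | 0.934 | 6.6% | 8.3% | 22 | 0.947 | 0.952 |

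Simulation A: 150 patients, between-patient SD 1 on the log scale, 400 runs per r. Simulation B: 128 patients, 7 visits, rate ratio exp(0.4), between-patient log-variance 0.8, 20% structural zeros, 300 runs per r. Both fitted a negative binomial model to patient totals, with and without the covariate. Neither fitted the longitudinal model of SAP 6.2.3, so they indicate scale only.

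Taking the formula and the model-SE ratios together, the SE falls by about 0%, 1–2%, 3–4% and 5–7%.

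The empirical SD of the estimate fell by more at the higher correlations: 3%, 7% and 10% in A, and 1%, 6% and 9% in B. The falls in A at every r, and in B at r = 0.3 and 0.4, exceed the s = 1 ceiling of the formula, and they rest on a few hundred runs on totals. They are not used for the size. The model SE is what sets the reported interval.

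**4. Power.** If the true effect were small enough for 80% unadjusted power, adjusted power = Φ[(1.960 + 0.842)/sqrt(1 − r²) − 1.960]. This gives 80%, 81.6%, 83.6% and 86.4% for r = 0, 0.2, 0.3 and 0.4. These are upper values, because they take s = 1. At the planned effect, power starts at 99.9% and has nowhere to go.

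**The case against.** The case for leaving the plan alone is substantial, and most of it stands.

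- **No error and no bias.** The model is pre-specified and adjusts for the stratification factor. Randomisation means that omitting a prognostic covariate does not bias the comparison, and nothing in the protocol calls for PSM_BL. This stands.
- **The loss is unproven.** A reader might infer that precision is certainly being thrown away. The documents do not support that: they report no correlation between PSM and side effects, and at r = 0 the gain is nil.
- **PSM is about medicines.** A reader might take it as a direct measure of proneness to side effects. The protocol describes a belief concerning medicines, lists PSM as a secondary outcome and never names it as a predictor for question 2. The treatment is needling, and several side effects listed in protocol 10.1 are local, such as bleeding, bruising and inflammation. A weak correlation is quite possible.
- **The covariate list is not obviously misapplied.** A reader might infer that the 6.4.3 list was chosen for pain. Protocol 11.3.2 offers those covariates for both 1a and 1b, so it was not specific to pain. Nor is using PSM_BL for its own follow-up value odd; that is ordinary ANCOVA.
- **The change is not entirely free.** A complete-case fit would drop the patients without P1 from an intention-to-treat analysis that was specified to need no missing-data handling (SAP 4.3). The model already has a convergence fallback.

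The last point can be answered. Whether P1 was completed is settled before allocation, so a simple fill-in for this covariate keeps every patient in the randomised comparison. The existing fallback covers convergence.

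**Conclusion.** The point holds as an inexpensive efficiency improvement to a primary analysis. PSM_BL is absent from all three question 2 models, it is measured before randomisation, and the protocol's description makes it a reasonable predictor of reported side effects.

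The likely benefit is small to modest: a fall in the model SE of the log ratio of about 1–2% at r = 0.2, 3–4% at r = 0.3, 5–7% at r = 0.4, and none at r = 0. This rests on an assumed r, an assumed between-patient share of 0.8, and simulations on totals rather than on the 6.2.3 model.

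A reader might also infer that question 2 is underpowered without the covariate. At the plan's own assumption it is not, since power is about 99.9%. The benefit is a narrower interval, or some power if the true effect is much smaller than planned.

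**What to change.** Make the change by a dated SAP revision before the statisticians see allocation (SAP 3.1 keeps them blind for the analysis):

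1. **SAP 6.2.3 and 6.6.3.** Add PSM_BL as a fixed effect in the count part. Fill the few missing values with the overall mean, and add a missing indicator if the model converges with it, so that no patient is dropped. The outcome still needs no imputation.
2. **SAP 6.4.3, question 2.** Add PSM_BL to the extended model and treat its missing values by the imputation already planned there. SAP 6.5 lists imputation predictors for questions 1a and 1b only, so name those for question 2 and include PSM_BL among them.
3. **If allocation has already been revealed.** Keep the present primary model and report the PSM_BL-adjusted result as a labelled sensitivity analysis.

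The cost is a few sentences of SAP text, one or two extra parameters, and a simple fill-in rule in a model that already has a convergence fallback. No new data are needed.
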